**FOR MALES ONLY**

| ***Interviewer reads:***“Now I am going to ask you questions about pregnancy, family planning, and your desire for children with your main partner.” |
| --- |

P1m. Has anyone in this HIV clinic ever spoken with you about contraceptives or family planning?

_____ 0. No *Skip to P2m*

_____ 1. Yes

*_____-1. Don’t know*

*_____-2. Refused*

P1ma. Which of the following staff at this HIV clinic have ever discussed contraceptives or family planning with you?

_____ 1. Health Care Provider (e.g, Clinical Officer, Doctor)

_____ 2. Nurse

_____ 3. Counselor

_____ 4. Pharmacist

_____ 5. Other (specify) ____________________

*_____-1. Don’t know*

*_____-2. Refused*

P2m. Is the person you consider to be your spouse or main partner currently pregnant?

_____ 0. No

_____ 1. Yes  *Skip to P8m*

_____ 2. No main partner  *Skip to Q1 in next section*

*_____-1. Don’t know*

*_____-2. Refused*

P3m. Do you want her to get pregnant in the next 6 months?

_____ 0. No

_____ 1. Yes

*_____-1. Don’t know*

*_____-2. Refused*

P4m. Does your spouse or main partner want to get pregnant in the next 6 months?

_____ 0. No

_____ 1. Yes

*_____-1. Don’t know*

*_____-2. Refused*

P5m. Have you ever used any method to avoid getting your spouse or partner(s) pregnant?

_____ 0. No  *Skip to P7m*

_____ 1. Yes

*_____-1. Don’t know*

*_____-2. Refused*

P6m. Are you, your spouse, or your main sex partner currently using any of these methods to avoid getting pregnant?

|  | **No** | **Yes** | *Don’t know* | *Refused* |
| --- | --- | --- | --- | --- |
| a. Pill | 0 | 1 | *-1* | *-2* |
| b. IUD (Intra-Uterine Device) | 0 | 1 | *-1* | *-2* |
| c. Injectable | 0 | 1 | *-1* | *-2* |
| d. Implants | 0 | 1 | *-1* | *-2* |
| e. Condom | 0 | 1 | *-1* | *-2* |
| f. Diaphragm | 0 | 1 | *-1* | *-2* |
| g. Foam/jelly | 0 | 1 | *-1* | *-2* |
| h. Lactational amenorrhea | 0 | 1 | *-1* | *-2* |
| i. Rhythm Method | 0 | 1 | *-1* | *-2* |
| j. Withdrawl | 0 | 1 | *-1* | *-2* |
| k. Female Sterilization | 0 | 1 | *-1* | *-2* |
| l. Male Sterilization | 0 | 1 | *-1* | *-2* |
| m. Other (Specify) ______________________ | 0 | 1 | *-1* | *-2* |

 **If NO to ALL of above, then ask P7m. Otherwise Skip** **P10m.**

P7m. I am going to read you some reasons people sometimes give for not using any method to avoid getting pregnant. For each of these, please tell me if this is a reason why you and your partner are not using any method.

|  | **No** | **Yes** | ***Don’t know*** | ***Refused*** |
| --- | --- | --- | --- | --- |
| a. I want to have children | 0 | 1 | *-1* | *-2* |
| b. My partner or I cannot get pregnant | 0 | 1 | *-1* | *-2* |
| c. I do not like using condoms | 0 | 1 | *-1* | *-2* |
| d. My partner does not like using condoms | 0 | 1 | *-1* | *-2* |
| e. My partner does not like the side effects of contraceptives | 0 | 1 | *-1* | *-2* |
| f. Contraceptives are inconvenient | 0 | 1 | *-1* | *-2* |
| g. My partner does not like the contraceptive methods that are available | 0 | 1 | *-1* | *-2* |
| h. Contraceptives are too hard for my partner to get | 0 | 1 | *-1* | *-2* |
| i. My religion does not allow me to use contraceptives | 0 | 1 | *-1* | *-2* |
| j. Contraceptives cost too much | 0 | 1 | *-1* | *-2* |
| k. My partner opposes using contraceptives | 0 | 1 | *-1* | *-2* |
| l. Contraceptives have never been offered to my partner | 0 | 1 | *-1* | *-2* |
| m. I do not know enough about contraceptives to know what to use or for my partner to use | 0 | 1 | *-1* | *-2* |
| n. I just have not thought about using contraceptives | 0 | 1 | *-1* | *-2* |
| o. Other (Specify)  ________________________________  ________________________________ | 0 | 1 | *-1* | *-2* |

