Project enrollment will occur over of a 2-3 month period at both intervention and comparison clinics. Following completion of the baseline data collection, the intervention will be implemented at the intervention clinics. Because of the baseline data collection period, the 6-month follow-up will be scheduled for a time estimated to be 6-months after the intervention is integrated into the clinic, so that all intervention clinic participants will have an opportunity to be exposed to the intervention following staff training and implementation. To make the intervention and comparison clinic project procedures as similar as possible, the intervention and comparison clinic 6-month follow-up interviews will occur during the same time period. The same battery of questionnaires will be administered to participants at the 6- and 12-month follow-up interviews, with the exception of some of the sociodemographic questions and items asking about whether something had “ever” happened. At each follow up interview, participants will be offered a soda or other drink and reimbursed for travel costs to the clinic upon completion of the interviews.

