**FOR MALES: GO TO QUESTION P1m ON PAGE 38**

**FOR FEMALES ONLY**

P1f. Has anyone in this HIV clinic ever spoken with you about contraceptives or family planning?

_____ 0. No *Skip to P2f*

_____ 1. Yes

*_____-1. Don’t know*

*_____-2. Refused*

P1fa. Which of the following staff at this HIV clinic have ever discussed contraceptives or family planning with you?

_____ 1. Health Care Provider (e.g, Clinical Officer, Doctor)

_____ 2. Nurse

_____ 3. Counselor

_____ 4. Pharmacist

_____ 5. Other (specify) ____________________

*_____-1. Don’t know*

*_____-2. Refused*

P2f. Are you pregnant now?

_____ 0. No

_____ 1. Yes  *Skip to P11f*

*_____-1. Don’t know*

*_____-2. Refused*

P3f. Do you want to get pregnant in the next 6 months?

_____ 0. No

_____ 1. Yes

*_____-1. Don’t know*

*_____-2. Refused*

P4f. Does your spouse or main sex partner want you to get pregnant in the next 6 months?

_____ 0. No

_____ 1. Yes

_____ 2. Don’t have a spouse or main sex partner

*_____-1. Don’t know*

*_____-2. Refused*

P5f. Have you ever used any method to avoid getting pregnant?

_____ 0. No

_____ 1. Yes

*_____-1. Don’t know*

*_____-2. Refused*

P6f. Are you currently using any of these methods to avoid getting pregnant?

|  | **No** | **Yes** | *Don’t know* | *Refused* |
| --- | --- | --- | --- | --- |
| a. Pill | 0 | 1 | -1 | -2 |
| b. IUD (Intra-Uterine Device) | 0 | 1 | -1 | -2 |
| c. Injectable | 0 | 1 | -1 | -2 |
| d. Implants | 0 | 1 | -1 | -2 |
| e. Condom | 0 | 1 | -1 | -2 |
| f. Diaphragm | 0 | 1 | -1 | -2 |
| g. Foam/jelly | 0 | 1 | -1 | -2 |
| h. Lactational amenorrhea | 0 | 1 | -1 | -2 |
| i. Rhythm Method | 0 | 1 | -1 | -2 |
| j. Withdrawl | 0 | 1 | -1 | -2 |
| k. Female Sterilization | 0 | 1 | -1 | -2 |
| l. Male Sterilization | 0 | 1 | -1 | -2 |
| m. Other (Specify) ______________________ | 0 | 1 | -1 | -2 |

 **If NO to ALL of above, then ask P7f. Otherwise Skip** **P8f.**

P7f. I am going to read you some reasons people sometimes give for not using any method to avoid getting pregnant. For each of these, please tell me if this is a reason why you are not using any method.

|  | **No** | **Yes** | *Don’t know* | *Refused* |
| --- | --- | --- | --- | --- |
| a. I want to have children | 0 | 1 | -1 | -2 |
| b. My partner or I cannot get pregnant | 0 | 1 | -1 | -2 |
| c. I do not like the side effects of contraceptives | 0 | 1 | -1 | -2 |
| d. Contraceptives are inconvenient | 0 | 1 | -1 | -2 |

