***AFTER ANSWERING P7m, SKIP TO P10m.***

P8m. How many months pregnant is your spouse or main partner now?

__________ # months pregnant

*_____-1. Don’t know*

*_____-2. Refused*

P9m. At the time your spouse or main partner became pregnant, did you want her to become pregnant *then*, did you want to wait until *later*, or did you *not want* to have any (more) children?

_____ 1. Then

_____ 2. Later

_____ 3. Not at all

*_____-1. Don’t know*

*_____-2. Refused*

P10m. In your relationship with your spouse or main partner, who decides if or when you should have more children? *[Tick one.]*

_____ 1. I do

_____ 2. My partner does

_____ 3. We decide together

_____ 4. My extended family does

_____ 5. No one really decides, we just let whatever is going to

happen, happen

_____ 6. No opinion

_____ 7. Other (Specify) ________________________

*_____-1. Don’t know*

*_____-2. Refused*

P11m. Have you talked with your spouse or main partner about contraceptives or planning your family in the past month?

_____ 0. No

_____ 1. Yes

*_____-1. Don’t know*

*_____-2. Refused*

P12m. How confident are you that you could talk with your spouse or main partner in the next month about contraceptives or planning your family?

_____ 1. Very confident

_____ 2. Confident

_____ 3. Somewhat confident

_____ 4. Not at all confident

*_____-1. Don’t know*

*_____-2. Refused*

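### In the male family planning section, 'No' at P5m skips the only question on the couple's current contraception, so female-controlled methods can go unrecorded

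*Protocol*

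**What the plan says.** The Protocol Summary lists contraceptive use among the patient-level outcomes. The description of the patient questionnaire under Study instruments says men will be asked adapted versions of the women's family planning items, covering their partner's status and needs.

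In Appendix H, Family Planning, males, the sequence is as follows.

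- P2m asks whether the spouse or main partner is pregnant. 'Yes' goes to P8m. Men with no main partner leave the section.
- The gate item is "P5m. Have you ever used any method to avoid getting your spouse or partner(s) pregnant". 'No' carries an instruction to go to P7m. 'Yes', 'Don't know' and 'Refused' carry no skip.
- P6m asks: "Are you, your spouse, or your main sex partner currently using any of these methods to avoid getting pregnant". The list includes pill, IUD, injectable, implants, condom and sterilization of either partner.
- The instruction under P6m is "If NO to ALL of above, then ask P7m".
- P7m reads out reasons and says "please tell me if this is a reason why you and your partner are not using any method".
- The routing then is "AFTER ANSWERING P7m, SKIP TO P10m".

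In the female version, "P5f. Have you ever used any method to avoid getting pregnant" has no skip on any answer.

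The Data collection section says the follow-up interviews use the same questionnaires "with the exception of some of the sociodemographic questions and items asking about whether something had “ever” happened".

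**The concern.** The gate and the item behind it ask about different things. P5m concerns the man's own behaviour at any time in the past. P6m concerns what either member of the couple is doing now. A 'No' to the first does not imply a 'No' to the second. The gap falls on the methods a woman uses without the man doing anything: pill, injectable, implant, IUD and female sterilization.

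For an affected man the questionnaire holds no value for the couple's current use, on an outcome the protocol lists. A question never asked cannot be recovered in analysis. Spouses and identified partners of participants are excluded from enrolment, so a partner's own study interview cannot fill the gap.

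**Working it through.** No power or sample-size figure is involved. The check is a trace of the skip pattern, followed by an illustration on assumed inputs.

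**Step 1. Male path.** Take a man whose main partner is not pregnant and uses an injectable, and who has never used a method himself.

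| Item | What happens |
| --- | --- |
| P2m | 'No'; continues |
| P3m, P4m | Pregnancy wishes; continues |
| P5m | 'No'; sent to P7m |
| P6m a to m | Not asked; blank |
| P7m | Asked why the couple uses no method |
| P10m to P12m | Decision-making and communication only |

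P8m and P9m are for men with a pregnant partner. No male item after P6m asks for the current method. The P7m reasons include none that says the partner already uses one, so only the free-text 'Other' line could reveal it.

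**Step 2. Who else reaches P7m.** Under the instruction below P6m, only men who said 'No' to every method. The P5m skip therefore puts men whose couple's status is unknown on the same path as men whose non-use has been confirmed.

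**Step 3. Female path.** A woman who is not pregnant answers P5f and goes on to P6f whatever she said. P7f is asked only if every P6f answer is 'No'. Current use is thus ungated in women and gated in men.

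**Step 4. Follow-up.** The Data collection section does not name the omitted 'ever' items, so there are two cases.

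- P5m is kept: the gap recurs at baseline, 6 and 12 months.
- P5m is omitted: P6m is gated at baseline and open at 6 and 12 months. Male-reported use is then not comparable between baseline and follow-up. The Data analysis plan enters the baseline value of the outcome as a covariate, and for these men it would be blank.

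**Step 5. Illustration of size.** The protocol gives neither input, so both are assumptions. Let s be the share of men reaching P5m who answer 'No', and q the share of those men whose partner uses a female-controlled method. The share of couples whose use goes unrecorded is s × q.

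- s = 10%, q = 10%: 0.10 × 0.10 = 0.01, or 1 percentage point.
- s = 40%, q = 30%: 0.40 × 0.30 = 0.12, or 12 percentage points.

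The protocol aims for equal numbers of men and women, so there are at most about 3600 / 2 = 1800 men. That gives 1800 × 0.01 = 18 to 1800 × 0.12 = 216 men. These counts are too high for the assumed shares, because men with no main partner or a pregnant partner never reach P5m.

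**The case against.** Several stronger readings are tempting, and the protocol does not support them.

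**That these couples are recorded as non-users.** P6m is left blank, not coded 'No', and the protocol states no rule for the blank. Such a rule could sit in an analysis plan that is not shown. Non-use is implied by the routing only.

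**That every man with a contracepting partner is lost.** The lead-in to the male items is about family planning with the main partner, and P5m speaks of any method. A man may count his wife's injections and answer 'Yes'. 'Don't know' and 'Refused' also continue to P6m.

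**That baseline and follow-up certainly measure different things.** This depends on P5m being dropped, which is not stated. Even then the change is the same in both arms. It would weaken the baseline covariate and cost precision, but would not by itself bias the randomised comparison.

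**That the loss biases towards no effect.** Missed uptake of female methods in the intervention arm would pull that way. But the package also gives out condoms. If P5m is kept, more intervention-arm men may come to answer 'Yes' and so be asked P6m, which would raise recorded use in that arm. Neither direction is established.

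Three further points limit the weight. The service-delivery hypothesis concerns counselling and services provided, and the Clinic Services Form counts pills and injections given to HIV-positive women at the clinic. The package supplies those methods to women patients, while male patients are counselled or referred. The Patient Medical Chart Review Form (Appendix P, item 8) has a row for the spouse's or partner's methods at each visit. That row is only a partial substitute: it depends on what providers ask and write down, which may differ between trained and usual-care clinics.

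What stands is the routing itself. None of these points supplies the missing questionnaire answer.

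**Conclusion.** The point holds as a form defect in one male-reported item. 'No' at P5m bypasses the only male questionnaire item on the couple's current contraception, leaves it blank, and groups the man with confirmed non-users, while women face no such gate. It rests on one modest assumption: that some men read P5m as asking about their own use, which is what its wording says.

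The number affected and the effect on the arm comparison cannot be determined from the protocol. The 1 to 12 percentage points in the working only show what assumed inputs would imply. Comparability between baseline and follow-up is at risk only if P5m is among the omitted 'ever' items. The primary outcome, any unprotected sex in the past 3 months, and the sample size are untouched. The correction is still worth making, because it is nearly free and the answer cannot be reconstructed afterwards.

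**What to change.** Delete the instruction at P5m that sends 'No' to P7m. Ask P6m of every man who reaches P5m at baseline, 6 and 12 months, whether or not P5m itself is kept at follow-up. Ask P7m only if all P6m answers are 'No', as the instruction under P6m already requires.

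The cost is the removal of one skip instruction from the form, with the matching change to its translations and the entry database, and one extra item for the men who answer 'No'. No new instrument or analysis is needed.

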***AFTER ANSWERING P7m, SKIP TO P10m.***

P8m. How many months pregnant is your spouse or main partner now?

__________ # months pregnant

*_____-1. Don’t know*

*_____-2. Refused*

P9m. At the time your spouse or main partner became pregnant, did you want her to become pregnant *then*, did you want to wait until *later*, or did you *not want* to have any (more) children?

_____ 1. Then

_____ 2. Later

_____ 3. Not at all

*_____-1. Don’t know*

*_____-2. Refused*

P10m. In your relationship with your spouse or main partner, who decides if or when you should have more children? *[Tick one.]*

_____ 1. I do

_____ 2. My partner does

_____ 3. We decide together

_____ 4. My extended family does

_____ 5. No one really decides, we just let whatever is going to

happen, happen

_____ 6. No opinion

_____ 7. Other (Specify) ________________________

*_____-1. Don’t know*

*_____-2. Refused*

P11m. Have you talked with your spouse or main partner about contraceptives or planning your family in the past month?

_____ 0. No

_____ 1. Yes

*_____-1. Don’t know*

*_____-2. Refused*

P12m. How confident are you that you could talk with your spouse or main partner in the next month about contraceptives or planning your family?

_____ 1. Very confident

_____ 2. Confident

_____ 3. Somewhat confident

_____ 4. Not at all confident

*_____-1. Don’t know*

*_____-2. Refused*

**Prevention Services Received**

| ***Interviewer reads:*** “Now I am going to ask you questions about your experience with your visits to this HIV clinic during the past 6 months.” |
| --- |

**Health care provider**

Q1. In the past 6 months, on average about how long did you meet with the health care provider each time?

__________ minutes

*_____-1. Don’t know*

*_____-2. Refused*

Q2. During your visits over the past 6 months did you feel like you had enough time to discuss your health or other concerns with the health care provider?

_____ 0. No

_____ 1. Yes

*_____-1. Don’t know*

*_____-2. Refused*

Q3. When was the last time you met with a health care provider in this clinic?

*[If participant met with health care provider today, tick box below, otherwise fill in how long it has been.]*

⁮ Today

_____ 1. days ago

_____ 2. weeks ago

_____ 3. months ago

*_____-1. Don’t know*

*_____-2. Refused*

Q4. I am going to read you some topics your health care provider might have talked to you about during your visits in the past 6 months. Please tell me if your health care provider did or did not talk to you about these during your visits in the past 6 months.

*[****Interviewer:*** *Read each response option to participant. Read the “yes” and “no” answer choices aloud to the participant. Don’t read the “don’t remember” and “refused” answer choices aloud to the participant.]*

|  | **No** | **Yes** | *Don’t remember* | *Refused* |
| --- | --- | --- | --- | --- |
| a. Your health and any problems you are having | 0 | 1 | *-1* | *-2* |
| b. Taking ARV medications as prescribed *[only for those on ARVs]* | 0 | 1 | *-1* | *-2* |
| c. Whether you are (your partner is) pregnant or plan to get pregnant | 0 | 1 | *-1* | *-2* |
| d. Whether you were experiencing any genital discharge, genital ulcers, *[Females only]* or lower abdominal pain. | 0 | 1 | *-1* | *-2* |
| e. Counseling on family planning | 0 | 1 | *-1* | *-2* |
| f. Counseling on safer pregnancy | 0 | 1 | *-1* | *-2* |
| g. Disclosing HIV status to your spouse or partner(s) | 0 | 1 | *-1* | *-2* |
| h. Getting your sex partner(s) tested for HIV | 0 | 1 | *-1* | *-2* |
| i. Using condoms correctly and consistently | 0 | 1 | *-1* | *-2* |
| j. Reducing your number of sex partners | 0 | 1 | *-1* | *-2* |
| k. Reducing your alcohol use | 0 | 1 | *-1* | *-2* |
| l. Healthy/positive living | 0 | 1 | *-1* | *-2* |
| m. Setting an HIV prevention goal | 0 | 1 | *-1* | *-2* |
| n. Are there any other things you talked about that I did not mention?  ***If yes****:* Specify  _____________________________  _____________________________ | 0 | 1 | *-1* | *-2* |

Q5. How helpful has getting information on these topics from the health care providers been for you?

_____ 1. Very helpful

_____ 2. Somewhat helpful

_____ 3. Not helpful

*_____-1. Don’t know*

*_____-2. Refused*

Q6. I am going to read you a list of topics you may have discussed with your health care providers. For each one, please tell me whether you made any changes in what you did or what you discussed with your partner(s) after talking about this with your health care providers?

|  | **No** | **Yes** | *Don’t remember* | *Refused* |
| --- | --- | --- | --- | --- |
| a. Took ARV medications as prescribed *[only for those on ARVs]* | 0 | 1 | -1 | -2 |
| b. Disclosed HIV status to spouse or partner(s) | 0 | 1 | -1 | -2 |
| c. Got sex partner(s) tested for HIV | 0 | 1 | -1 | -2 |
| d. Used condoms correctly and consistently | 0 | 1 | -1 | -2 |
| e. Reduced number of sex partners | 0 | 1 | -1 | -2 |
| f. Addressed family planning issues (contraceptives or safer pregnancy) | 0 | 1 | -1 | -2 |
| g. Reduced alcohol use | 0 | 1 | -1 | -2 |
| h. Healthy/positive living | 0 | 1 | -1 | -2 |
| i. Anything else? Specify:  _________________________________ | 0 | 1 | -1 | -2 |

Q7. Some topics can be difficult to talk about, such as sexual behavior, condom use, and alcohol use. How comfortable do you feel discussing these topics with your health care provider?

_____ 1. Very comfortable

_____ 2. Comfortable

_____ 3. Neither comfortable nor uncomfortable

_____ 4. Uncomfortable

_____ 5. Very uncomfortable

*_____-1. Don’t know*

*_____-2. Refused*

Q8. During your visits with health care providers in the past 6 months, were you given condoms?

_____ 0. No  *Skip to Q8b*

_____ 1. Yes

*_____-1. Don’t know*

*_____-2. Refused*

Q8a. How many condoms were you given during your last visit?

__________ # condoms

*_____-1. Don’t know*

*_____-2. Refused*

Q8b. In the past 6 months, were condoms available for you to take in this clinic?

_____ 0. No

_____ 1. Yes

*_____-1. Don’t know*

*_____-2. Refused*

Q9. During your visits with health care providers in the past 6 months, did any health care provider refer you to…

|  | **No** | **Yes** | ***Don’t remember*** | ***Refused*** |
| --- | --- | --- | --- | --- |
| a. a counselor? | 0 | 1 | *-1* | *-2* |
| b. a family planning clinic different from this clinic? | 0 | 1 | *-1* | *-2* |
| c. a STI clinic different from this clinic? | 0 | 1 | *-1* | *-2* |
| d. any other clinic or service?  ***If yes****:* Specify  _____________________________________________  _____________________________________________ | 0 | 1 | *-1* | *-2* |

**Counselor**

| ***Interviewer reads:*** “Now I am going to ask you some questions about meeting with counselors at this clinic in the past 6 months. These questions are similar to the questions I just asked you, but instead of asking you about health care providers like doctors, medical officers, nurses, and pharmacists, I will be asking you only about your meetings with counselors.” |
| --- |

R1. In the past 6 months, how many times did you meet with a counselor when you came to this clinic?

__________ # times met with counselor  *If 0, skip to R1a*

 *If 1, skip to R2*

 *If 2 or more, skip to R1b*

*_____-1. Don’t know*

*_____-2. Refused*

R1a. Would it have been helpful to see a counselor?

_____ 0. No  *Skip to* **END**

_____ 1. Yes  *Skip to* **END**

*_____-1. Don’t know*  *Skip to* **END**

*_____-2. Refused*  *Skip to* **END**

R1b. Did you meet with the same counselor each time?

_____ 0. No

_____ 1. Yes

*_____-1. Don’t know*

*_____-2. Refused*

R2. Did you want to see a counselor more often?

_____ 0. No  *Skip to R3*

_____ 1. Yes

*_____-1. Don’t know*

*_____-2. Refused*

R2a.What kept you from seeing a counselor more often?

*[Read all options and tick all that apply.]*

_____ 1. My schedule was too busy

_____ 2. The counselor’s schedule was too busy

_____ 3. Not able to come to the clinic

_____ 4. I did not have anything to discuss with the

counselor

_____ 5. I did not know it was an option to meet more often

_____ 6. Other: Specify ___________

*_____ -1. Don’t know*

*_____ -2. Refused*

R3. During your visits over the past 6 months with the counselor(s), on average, about how long did you meet with the counselor each time?

__________ minutes

*_____-1. Don’t know*

*_____-2. Refused*

R4. During your visit over the past 6 months, did you feel like you had enough time to discuss your health or other concerns with the counselor(s)?

_____ 0. No

_____ 1. Yes

*_____-1. Don’t know*

*_____-2. Refused*

R5. When was the last time you met with a counselor in this clinic?

*[If participant met with counselor today, tick box below, otherwise fill in how long it has been.]*

⁮ Today

_____ 1. days ago

_____ 2. weeks ago

_____ 3. months ago

*_____-1. Don’t know*

*_____-2. Refused*

R6. I am going to read you some topics your counselor(s) might have talked with you about during your visits in the past 6 months. Please tell me if your counselor(s) did or did not talk to you about these during your visits in the past 6 months.

[***Interviewer:*** *Read each response option to participant.]*

|  | **No** | **Yes** | ***Don’t remember*** | ***Refused*** |
| --- | --- | --- | --- | --- |
| a. Your health and any problems you are having now | 0 | 1 | *-1* | *-2* |
| b. Preparing for antiretroviral therapy *[only for those* ***not*** *on ART]* | 0 | 1 | *-1* | *-2* |
| c. Taking ARV medications as prescribed *[only for those on ARVs]* | 0 | 1 | *-1* | *-2* |
| d. Disclosing your HIV status to your spouse or partner(s) | 0 | 1 | *-1* | *-2* |
| e. Getting your sex partner(s) tested for HIV | 0 | 1 | *-1* | *-2* |
| f. Using condoms correctly and consistently | 0 | 1 | *-1* | *-2* |
| g. Reducing your number of sex partners | 0 | 1 | *-1* | *-2* |
| h. Reducing your alcohol use | 0 | 1 | *-1* | *-2* |
| i. Healthy/positive living | 0 | 1 | *-1* | *-2* |
| j. Coping with HIV | 0 | 1 | *-1* | *-2* |
| k. Setting an HIV prevention goal | 0 | 1 | *-1* | *-2* |
| l. Are there any other things you talked about that I did not mention?  ***If yes****:* Specify _____________________________ __________________________ | 0 | 1 | *-1* | *-2* |
| m. Is there anything else you talked about?  ***If yes****:* Specify ____________________________ _____________________________ | 0 | 1 | *-1* | *-2* |

R7. How helpful has getting information on these topics from the counselors been for you?

_____ 1. Very helpful

_____ 2. Somewhat helpful

_____ 3. Not helpful

*_____-1. Don’t know*

*_____-2. Refused*

R8. I am going to read you a list of topics you may have discussed with the counselor. For each one, please tell me whether you made any changes in what you did or what you discussed with your partner(s) after talking about this with the counselor?

|  | **No** | **Yes** | *Don’t remember* | *Refused* |
| --- | --- | --- | --- | --- |
| a. Took ARV medications as prescribed *[only for those on ARVs]* | 0 | 1 | *-1* | *-2* |
| b. Disclosed HIV status to spouse or partner(s) | 0 | 1 | *-1* | *-2* |
| c. Got sex partner(s) tested for HIV | 0 | 1 | *-1* | *-2* |
| d. Used condoms correctly and consistently | 0 | 1 | *-1* | *-2* |
| e. Reduced number of sex partners | 0 | 1 | *-1* | *-2* |
| f. Addressed family planning issues (contraceptives or safer pregnancy) | 0 | 1 | *-1* | *-2* |
| g. Reduced alcohol use | 0 | 1 | *-1* | *-2* |
| h. Healthy/positive living | 0 | 1 | *-1* | *-2* |
| i. Anything else? Specify: _____________________________________ | 0 | 1 | *-1* | *-2* |

R9.Some topics can be difficult to talk about, such as sexual behavior, condom use, and alcohol use. How comfortable do you feel discussing these topics with the counselors?

_____ 1. Very comfortable

_____ 2. Comfortable

_____ 3. Neither comfortable nor uncomfortable

_____ 4. Uncomfortable

_____ 5. Very uncomfortable

*_____-1. Don’t know*

*_____-2. Refused*

R10. During your visits with a counselor(s) in the past 6 months, were you given condoms?

_____ 0. No  *Skip to* **END**

_____ 1. Yes

*_____-1. Don’t know*

*_____-2. Refused*

R10a. How many condoms were you given the last visit?

__________ # condoms

*_____-1. Don’t know*

*_____-2. Refused*

| ***Interviewer reads:* “**Thank you for taking the time to participate in this interview. We will need to make a follow-up appointment for you in six months for you. Do you have any questions or did you want to add anything else?” |
| --- |

